#### Individual randomized study

A sample of 440 HIV-positive men identified though mobile HTS at baseline will be randomized to either standard-of-care referral to ART or POC CD4 testing combined with personalized linkage to care. Randomization sequence will be generated in advance by the statistical center, using the Mersenne-Twister random number generator with seed derived from current system time. Randomization assignments will be placed into sealed tamper-proof numbered envelopes according to the generated sequence and released to study counselors in small batches. The envelopes will be used in the assigned order to reveal randomization results for individual participants. Lost or misplaced envelopes will be registered and tracked. The randomization sequence will be fully non-predictable.

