#### Male-focused and delivered mobile HTS (Component 2)

The mobile HIV-testing services teams coordinate with CBM teams to ensure that testing happens according to the testing schedule. Copies of the testing schedule are distributed to community working groups, community-based outreach volunteers, local police stations, local health centers, and other community centers deemed appropriate by the study team.

Two HTS teams (four male nurse counselors and one driver per team) deliver easy-to-access mobile HIV testing through two mobile caravans. A mobile HTS team circulates through a range of male-centered locations in the community on a regular schedule of days and times suitable for men. Two teams serve the four intervention communities, with each team being responsible for two intervention communities over the course of the intervention. The team is supervised by a Counselor Supervisor.

CBMs are stationed in the vicinity of the men-centered spaces and engage men individually and in groups about the study. Mobilizers also inform men that a small incentive of R50 cell phone airtime (approximately US$5) would be received at completion of testing, regardless of HIV status. Other men in the vicinity of the mobile facility, but not necessarily frequenting the venues, are also encouraged to test by study staff. Recruited men are handed over to the study counselor at the mobile caravan for a fuller explanation of the study, informed consent, and completion of the HTS process.

Participants give consent for on-site POC procedures for screening for HIV and non-communicable diseases (NCDs) using rapid and POC tests. No specimens are retained for HIV and NCDs testing. In the event of a discordant HIV test result, a Dry Blood Spot (DBS) specimen will be collected from the participant for a laboratory confirmatory test to confirm serostatus. No specimens are retained for confirmatory tests. Participants who are eligible for enrolment (HIV-positive and not on antiretroviral treatment) and who consent to enrolment provide a DBS for baseline VL measures. Consent is provided for participants to be re-contacted at three and six months for study contact visits and for an exit visit at nine months after enrolment where participant exit survey data and end-line VL will be collected. Participants consent for their data to be stored and for secondary use of their data if such use is approved by the REC.

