#### Aim 2: Individually Randomized component

We will test the hypothesis that the proportion of HIV-positive men who were linked to care and maintained with undetectable VL nine months after enrolment will be the same in the POC + PLC arm as in the standard-of-care arm. The analysis will be based on men who were randomized and who completed the follow-up visit. We will use asymptotic tests for log odds ratios performed at the two-sided level of 0.05. Confidence intervals will be obtained by the same method.

#### Power calculations for Aim 2

Assuming that the rates of linkage to care and undetectable VL are 33% in the standard arm and 50% in the POC + PLC arm (odds ratio 2.0), the sample size of 175 individuals per arm yields 88% power to detect the effect of POC + PLC over standard of care. Adjusting for 20% attrition yields the sample size of 220 per arm.

#### Secondary analyses for Aim 2

We will carefully investigate the effect on attrition on the primary analysis of Aim 2. We will compare the men who do and do not present for the final visit to assess potential bias in the analysis of the primary endpoint of Aim 2. We will evaluate the attrition effect by multiple imputation of missing data using baseline characteristics of the individuals. We will compare HIV-positive men identified in Aim 1 who do and do not enroll in the Aim 2 study.

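### The primary Aim 2 test is valid but names no covariate; adjusting for the baseline viral load already collected would add modest power at almost no cost

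*Protocol article*

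**What the plan says.** The section on male-focused mobile HTS (Component 2) sets eligibility and the baseline specimen together: "Participants who are eligible for enrolment (HIV-positive and not on antiretroviral treatment) and who consent to enrolment provide a DBS for baseline VL measures". It sets no VL threshold for entry.

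The data analysis section for Aim 2 defines the tested outcome as "the proportion of HIV-positive men who were linked to care and maintained with undetectable VL nine months after enrolment", in randomized men who complete follow-up. The method is: "We will use asymptotic tests for log odds ratios performed at the two-sided level of 0.05". Confidence intervals come from the same method. No covariate or stratum is named.

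The power statement assumes 33% against 50% and an odds ratio of 2.0: "the sample size of 175 individuals per arm yields 88% power to detect the effect of POC + PLC over standard of care". It continues: "Adjusting for 20% attrition yields the sample size of 220 per arm". The section on the individual randomized study gives the matching total of 440 and describes no stratification by community.

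The only stated uses of baseline information are in the secondary analyses: multiple imputation from unspecified baseline characteristics, and a comparison of men with and without a final visit. Neither names VL.

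**The concern.** The tested outcome includes undetectable VL at nine months, and VL is also measured at enrolment. A baseline value of the variable that defines success is a natural covariate, yet the primary test does not use it.

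Two things follow. First, a man already undetectable at entry (through undisclosed treatment or natural control) can count as a success without either arm having changed his VL, provided he links to care. Such men pull the two arms' rates together. Second, men come from the four intervention communities, and extended clinic hours are offered only at some clinics. Neither the randomization nor the test takes account of community, so a chance imbalance in VL or community would go uncorrected in the primary result.

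At stake are some power and robustness to imbalance. The validity of the test is not in question.

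**Working it through.** **Inputs from the article.** 175 evaluable men per arm, 33% and 50%, two-sided 0.05, 20% attrition.

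**Inputs assumed, because the article gives none.** q is the share undetectable at entry (2% to 20%). u is the rate of success on the composite among those men (60% to 90%). Since the composite also requires linkage, u could be lower. If it came close to the other men's rates, the gain below would vanish.

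**1. The plan's own figure.** For an unadjusted Wald test, SE = √[1/(n·p0(1−p0)) + 1/(n·p1(1−p1))] and power = Φ(log OR/SE − 1.96).
- 33% v 50%: log OR = ln 2.03 = 0.708; SE = √(1/38.69 + 1/43.75) = 0.2207; power = Φ(3.209 − 1.96) = 89.4%.
- 1/3 v 1/2 (odds ratio exactly 2.0): log OR = 0.693; SE = 0.2204; power = Φ(3.145 − 1.96) = 88.2%, matching the stated 88%.
- 175/0.8 = 218.75, so 219, against 220 stated.

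The sample size is sound, and the planning calculation is that of an unadjusted test.

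**2. Power with a baseline-undetectable term.** Expected information from a logistic model with arm and this one binary term, n = 175 per arm. Ranges run over u = 60% to 90%.
- Scenario A: 33% and 50% are the rates in all enrolled men, with a common conditional odds ratio.
- Scenario B: 33% and 50% hold only in men detectable at entry, and there is no effect in the rest.

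| q | A unadjusted | A adjusted | B unadjusted | B adjusted |
|---|---|---|---|---|
| 2% | 89.4% | 89.6–90.0% | 88.0–88.1% | 88.2–88.6% |
| 5% | 89.4% | 89.8–91.0% | 85.8–86.0% | 86.2–87.2% |
| 10% | 89.4% | 90.3–92.6% | 81.6–82.0% | 82.5–84.7% |
| 20% | 89.4% | 91.4–96.1% | 71.8–72.2% | 73.1–78.4% |

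At the same u, the gain is 0.1 to 1.6 points for q up to 5%, 0.5 to 3.2 at 10% and 0.9 to 6.7 at 20%. In scenario B at 10%, dilution costs about 7 to 8 points (89.4% to about 82%), and adjustment recovers only 0.5 to 3 of them.

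**3. Which effect scale.** In scenario A with q = 10% and u = 80%, adjustment moves the conditional odds ratio from 2.03 to 2.18 and its SE up from 0.2207 to 0.2325. Power rises to 91.7%, but the interval on the log scale widens, because odds ratios are non-collapsible. A gain in precision for the planned marginal comparison needs a standardized effect.

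**4. Standardized risk difference.** Scenario B, q = 10%, u = 90%.
- Marginal rates: 0.9×0.33 + 0.1×0.90 = 0.387 and 0.9×0.50 + 0.1×0.90 = 0.540; difference 0.153.
- Unadjusted variance: (0.387×0.613 + 0.540×0.460)/175 = 0.4856/175; SE 0.0527; power Φ(2.904 − 1.96) = 0.83.
- Standardized over baseline status: within-stratum variances 0.9×0.2211 + 0.1×0.09 = 0.2080 and 0.9×0.25 + 0.1×0.09 = 0.2340. Variance = 0.4420/175 + (0.9×0.1×0.17²)/350; SE 0.0503; power Φ(3.040 − 1.96) = 0.86.

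The same steps at q = 5% give 0.87 unadjusted and 0.885 standardized.

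**5. Not computed.** The further contribution of log10 VL among detectable men, and of community, cannot be derived from the article.

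**The case against.** The strongest case against is that the article names a family of tests and does not rule out covariates. These are often left to an analysis plan, and none was available here. This stands in part: it cannot be said that adjustment is excluded. But the article does fix the hypothesis, analysis set, test, level and interval method, and its power matches the unadjusted test. The point is therefore about a stated choice and not only a gap.

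Several stronger readings are tempting, and the article does not support them.
- **Baseline VL is ignored altogether.** The imputation from baseline characteristics may include it. All that can be said is that no Aim 2 analysis names it.
- **A man undetectable at entry is automatically a success.** The tested outcome also requires linkage to care, and men on treatment are ineligible. The reading fits only the separately listed outcome of undetectable VL at exit.
- **The comparison is biased.** Men are individually randomized, so such men balance in expectation. The type I error of the unadjusted test holds without a VL or community term.
- **The stated power is wrong.** It reproduces. Power is lost only if the planning rates are taken to exclude men undetectable at entry, which the article does not say.
- **Adjustment gives a narrower interval for the odds ratio at no cost.** For a conditional odds ratio the SE rises.
- **The primary set should be limited to men detectable at baseline.** In scenario B this would give power of about 0.86 at 10% undetectable and 0.82 at 20%. But it changes the target population, removes randomized men on a laboratory result, makes an undetectable-at-baseline indicator impossible to fit, and alters the success rates that Aim 3 multiplies. It belongs in a sensitivity analysis.

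**Conclusion.** The point holds as a free improvement and not as an error. The planned Aim 2 test is valid and its sample size reproduces. It forgoes a modest gain that data already being collected would provide: roughly 0 to 2 power points if up to 5% of men are undetectable at entry, about 0.5 to 3 at 10%, and 1 to 7 at 20%. These figures rest on assumed shares and on an assumed 60% to 90% success rate among those men; the article gives neither. If the eligibility criterion works as intended, the lower end is the likelier one. The second benefit, protection against chance imbalance in VL and community under a randomization with no described strata, does not depend on the undetectable share but cannot be sized from the article.

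**What to change.** Keep the planned analysis set, with no exclusion on baseline VL. Then:
- **Primary test:** a logistic model of the nine-month composite on arm, adjusted for baseline log10 VL, an indicator for undetectable at baseline, and community. For undetectable men, set log10 VL to one fixed value such as the assay limit.
- **Reported effect:** the covariate-standardized marginal odds ratio and risk difference, with robust or delta-method confidence intervals.
- **Supportive:** the unadjusted log odds ratio as now written.
- **Sensitivity:** the same comparison in men detectable at baseline.
- **Descriptive:** the number undetectable at entry, by arm.

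The wording should also confirm that the enrolment blood spot is taken before allocation is revealed, which the article does not state, and say how a missing baseline VL is handled.

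The cost is analysis wording only: no new data, visits or sample size. Because the article says that the study statistician is not blinded, the model should be fixed in writing before outcome data are examined.

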#### POC CD4 testing with male-centered PLC

HIV-positive participants randomized into the PLC phase of the study receive POC CD4 testing. The study nurse conducts same-day CD4 testing by taking a small blood sample obtained from the participant’s fingertip by a lancet. The date of the HIV and CD4 test and symptoms reported by the participant are provided in a one-page letter to the clinic to facilitate ART initiation. At the end of the counseling session, the nurse counselor schedules a follow-up visit for the participant and their study assigned PLC clinic-based champion (CBC). The CBC coordinates schedules with the participant and visits the HIV clinic with the participant within two weeks of enrolment. PLC services are tailored for individual clients and include pro-active case-management counseling to discuss and reduce barriers to linkage to care, adherence, and the importance of disclosure. It also comprises CBC accompaniment of the participant to help them navigate the health systems and extended hours access to the ART clinic.

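### The Aim 2 test, interval and 88% power make no allowance for clustering by clinic-based champion in the PLC arm; if outcomes correlate within champion, the standard error is understated

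*Protocol article*

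**What the plan says.** Aim 2 randomizes individual men (Individual randomized study: "A sample of 440 HIV-positive men identified though mobile HTS at baseline will be randomized"). Under Data analysis, Aim 2, the arms are compared as follows: "We will use asymptotic tests for log odds ratios performed at the two-sided level of 0.05". On the interval: "Confidence intervals will be obtained by the same method". No term for champion, clinic or community is named.

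The power section assumes rates of "33% in the standard arm and 50% in the POC + PLC arm (odds ratio 2.0") and concludes that "the sample size of 175 individuals per arm yields 88% power to detect the effect of POC + PLC over standard of care". It then adds: "Adjusting for 20% attrition yields the sample size of 220 per arm". No design effect appears.

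Delivery differs between the arms. In the section on POC CD4 testing with male-centered PLC, each man is given a "study assigned PLC clinic-based champion (CBC"). The sections on accompaniment and regular follow-ups have the champion go with the man to the clinic or meet him there, see him again later if he has not established care, and arrange support groups with other men. Under HIV standard of care, the comparison group receives a results slip that serves as a referral letter, and each man chooses his own clinic. No champion is involved.

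**The concern.** This is a partially nested design: men in one arm share providers and men in the other do not. The treatment itself creates the grouping, so individual randomization does not balance it as it would a clinic or community effect that existed beforehand. If some champions are more successful than others, men with the same champion have correlated outcomes, and the PLC proportion varies more than a binomial calculation with 175 independent men allows.

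At stake are the coverage of the Aim 2 interval, the nominal 5% level and the 88% power. The Aim 3 section multiplies the Aim 2 success rates into overall rates, with intervals, and projects numbers of men treated from population size and prevalence. That use reaches beyond the champions the study happened to employ. Aim 1, by contrast, analyses community-level proportions and carries a between-community variance of 0.007; Aim 2 carries nothing comparable.

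**Working it through.** **1. Reproduce the stated power.** Inputs: 175 per arm, two-sided 0.05, 33% versus 50% (Power calculations for Aim 2). An odds ratio of exactly 2.0 corresponds to 1/3 versus 1/2.

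SE² = 1/(n·p1·q1) + 1/(n·p2·q2) = 1/(175 × 1/3 × 2/3) + 1/(175 × 0.25) = 0.02571 + 0.02286 = 0.04857, so SE = 0.2204.

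Power = Φ(ln 2 / 0.2204 − 1.96) = Φ(3.145 − 1.96) = 88.2%. With 33% in place of 1/3 it is 89.4%. The stated 88% is therefore the independent-observations figure. For attrition, 175/0.80 = 218.75, consistent with 220.

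**2. Add clustering in the PLC arm only.** The number of champions k and the ICC are not in the article. Both are assumed here: k from 4 to 20, ICC from 0 to 0.05. As an order-of-magnitude guide only, the Aim 1 variance implies 0.007/(0.3 × 0.7) = 0.033, but that concerns communities and testing, not champions and viral load.

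Men per champion: m = 175/k. Design effect in the PLC arm: DE = 1 + (m − 1) × ICC. With equal arm rates, true SE / planned SE = √((1 + DE)/2), and actual level = 2(1 − Φ(1.96/ratio)).

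Worked case, k = 8 and ICC 0.02: m = 21.9, DE = 1 + 20.9 × 0.02 = 1.417, ratio = √(2.417/2) = 1.099, level = 2(1 − Φ(1.783)) = 7.5%.

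| Champions | ICC 0 | ICC 0.01 | ICC 0.02 | ICC 0.05 |
|---|---|---|---|---|
| 20 | 5.0% | 5.4% | 5.9% | 7.3% |
| 12 | 5.0% | 5.8% | 6.6% | 9.0% |
| 8 | 5.0% | 6.2% | 7.5% | 11.2% |
| 4 | 5.0% | 7.5% | 10.1% | 17.3% |

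Simulation with beta-distributed champion success rates agrees to within a few tenths of a point. For ICC 0.01 to 0.05 it gives about 5.4–7.1% with 20 champions, 5.8–8.7% with 12, 6.1–11.2% with 8 and 7.4–17% with 4. With ICC 0 it gives about 5%.

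**3. What a partially nested test would do.** Simulated champion-level variance in the PLC arm, individual variance in standard of care, Satterthwaite degrees of freedom. Its size for ICC 0.01 to 0.05 is 5.1–5.4% with 8 or 12 champions and 5.7–6.5% with 4. Its power at 1/3 versus 1/2:

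| Champions | ICC 0 | ICC 0.01 | ICC 0.05 |
|---|---|---|---|
| 12 | 0.87 | 0.85 | 0.75 |
| 8 | 0.86 | 0.82 | 0.67 |
| 4 | 0.81 | 0.71 | 0.43 |

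With 8 or more champions the method costs one or two points of power when there is no champion effect. With 4 it costs about seven points even then.

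**The case against.** A reader might infer that the Aim 2 type I error does exceed 5%. The article does not support that. It gives no number of champions, caseload, allocation rule or ICC, and it does not say that champions differ in success. With ICC 0 the planned test holds its level. If PLC changes no man's outcome, champions cannot induce correlation, and the level again holds. If the question is confined to the champions actually used, the test is also valid: in simulation with the standard-of-care rate set to those champions' mean, size was 0.045–0.051. These points stand, and they make the finding conditional. They do not remove it, because the stated hypothesis is equality of two proportions rather than no effect on any man, and Aim 3 projects beyond the champions employed.

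Contact may also be too light for a large ICC. The first accompaniment falls within two weeks, later visits are conditional, extended hours are negotiated by the team leader, and the outcome is measured at nine months. That is a fair reason to doubt the top of the range, not to assume zero.

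The nested analysis has limits too. If champions are tied to clinics that standard-of-care men also use, it will count some shared clinic variation as champion variance and be conservative. With 4 champions it loses much power and still slightly exceeds 5%. This stands and limits the remedy.

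Finally, an analysis plan that is not shown may address provider clustering, and nothing says the champion identifier goes unrecorded. The article nevertheless states the test, interval and power, and as stated they assume independence.

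**Conclusion.** The concern holds in conditional form. The Aim 2 test, interval and power treat all men as independent although delivery in one arm is grouped by champion. The standard error is understated if two conditions are met: a positive within-champion correlation with several men per champion, and inference meant to extend past those champions. Under an assumed ICC of 0.01 to 0.05, the departure ranges from negligible (5.4% at ICC 0.01 with 20 champions) to serious (about 17% at ICC 0.05 with 4). The largest value pairs the fewest champions with the highest ICC and should not be read as the expected one. The 88% power is arithmetically correct, but only with no champion effect.

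**What to change.** - Keep the champion identifier in the analysis dataset for every PLC man, and state the number of champions and their caseload.
- Report the Aim 2 effect and interval from a partially nested analysis, with champion as cluster in the PLC arm only and small-sample degrees of freedom. Make it primary if there are about 8 or more champions. With fewer, prespecify it as a sensitivity analysis beside the planned log odds ratio test.
- State that 88% power holds only with no champion effect, and give the range for ICC 0.01 to 0.05: about 0.85–0.75 with 12 champions, 0.82–0.67 with 8, 0.71–0.43 with 4.

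This needs one variable and a few sentences, and no extra participants. Enrolment was expected to continue to 30 April 2020, so at publication the choice could still be fixed before the final analysis. The downside is a wider interval and a less favourable stated power. Both are small with about 8 or more champions and a low ICC, and substantial with very few champions.

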#### Measurement of Aim 2 outcomes

This uses information collected at the nine-month exit interview.
We will conduct facility level chart abstraction to confirm linkage to care for those enrolled in the study and laboratory DBS VL assessment to establish viral suppression.

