#### Aim 3: Integrating the outcomes of the structural and individual-level interventions

We will estimate the joint effect of the structural and individual-level interventions on the percentage of HIV-positive men who are effectively treated (tested, linked to care, and maintained with undetectable VL) by estimating the percentage of HIV-positive men who have been tested in male-centered mobile HTS versus control arms using data on HIV testing and HIV status of the post-intervention assessment participants from Aim 1, and estimating success rates of undetectable VL in SOC and POC + PLC arms in Aim 2 (adjusted for attrition if needed). These estimates will be multiplied to estimate overall success rates of undetectable VL among HIV-positive men in all four combinations of the two interventions. Confidence intervals will be also calculated. We will assume that the interventions do not interact with each other since each targets a different stage in the process leading to successful HIV treatment of HIV-positive men. Given population size and HIV prevalence, we will be able to estimate the number of men who would be identified, treated, and maintained on treatment under each of the possible intervention combinations. A sensitivity analysis will be performed to evaluate the impact of potential non-independence of intervention effects.

A full factorial design is not feasible because one of the interventions is applied at the community level and the other at the individual level; success at the first of the interventions (being tested) is a condition of enrolment into the other intervention. This brings bias into the randomization of the community-level intervention. This design could only be conducted by randomizing whole communities to the four combinations of the interventions, but that would be too costly.

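### The Aim 2 attrition imputation names only baseline characteristics as inputs, although linkage, a required part of the outcome, may be known from charts for men who miss the nine-month visit

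*Protocol article*

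**What the plan says.** All references are to the protocol article.

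- **Outcome tested** (Data analysis, Aim 2): "the proportion of HIV-positive men who were linked to care and maintained with undetectable VL nine months after enrolment". A success therefore needs both linkage and suppression.
- **Primary analysis set** (same section): "The analysis will be based on men who were randomized and who completed the follow-up visit".
- **Attrition** (Power calculations for Aim 2): "Adjusting for 20% attrition yields the sample size of 220 per arm".
- **Check on attrition** (Secondary analyses for Aim 2): attenders are compared with non-attenders, and "We will evaluate the attrition effect by multiple imputation of missing data using baseline characteristics of the individuals".
- **Source of linkage** (Measurement of Aim 2 outcomes): "We will conduct facility level chart abstraction to confirm linkage to care for those enrolled in the study". The sentence before it says that the measurement draws on the nine-month exit interview.
- **Source of end-line VL** (Male-focused and delivered mobile HTS): a specimen taken at the exit visit, so it is missing when the visit is missed.
- **Later use** (Aim 3): the plan relies on "estimating success rates of undetectable VL in SOC and POC + PLC arms in Aim 2 (adjusted for attrition if needed").

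**The concern.** For a man who misses the exit visit, VL is unknown but linkage may be on record at a clinic. Linkage is both a necessary component of the outcome and probably its strongest predictor, since men enter Aim 2 only if they are not on treatment. The personalized linkage arm acts on linkage after baseline, so baseline data cannot carry that information.

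The imputation is the one named method that re-estimates the Aim 2 result under attrition. If its inputs say little about who entered care, it returns roughly the completers' rates and can look like reassurance without being any. If the adjusted rates are then used in Aim 3, the same error passes into the estimated yield of the combined interventions.

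**Working it through.** **1. The plan's own figures.** The planned rates are "33% in the standard arm and 50% in the POC + PLC arm (odds ratio 2.0"), with 175 men per arm analysed by this rule: "We will use asymptotic tests for log odds ratios performed at the two-sided level of 0.05". At an odds ratio of exactly 2.0 (1/3 vs 1/2):

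- SE = sqrt[1/(175 × 0.2222) + 1/(175 × 0.25)] = 0.220
- power = Φ(0.693/0.220 − 1.96) = 0.882, against 88% stated
- 175/0.80 = 218.75, so 219, against 220 stated

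The planning figures stand. At 20% attrition, 0.20 × 220 = 44 men per arm have no exit VL.

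**2. What baseline-only imputation returns.** Let L be the share linked, s the success rate among linked men, and m1 and m0 the probabilities of missing the exit visit for linked and unlinked men. Unlinked men cannot succeed.

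- True rate = L·s
- Attrition A = L·m1 + (1 − L)·m0
- Completers' rate = L·s·(1 − m1)/(1 − A)

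If baseline data are uninformative and the composite is imputed as one variable within arm, imputation returns the completers' rate in expectation.

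Assumptions not in the documents: L = 50% in standard of care (SOC) and 75% in POC + PLC (PLC); s = 0.66 and 0.667, so that L·s = 33% and 50%; and the drop-out probabilities below.

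| Scenario | SOC m1, m0 | PLC m1, m0 | SOC rate | PLC rate | Difference (truth 17.0) |
|---|---|---|---|---|---|
| (a) 20% attrition per arm, mostly unlinked men | 0.05, 0.35 | 0.10, 0.50 | 0.33 × 0.95/0.80 = 39.2% | 0.50 × 0.90/0.80 = 56.3% | 17.1 |
| (b) 20% per arm, all unlinked men | 0, 0.40 | 0, 0.80 | 0.33/0.80 = 41.3% | 0.50/0.80 = 62.5% | 21.3 |
| (c) 30% SOC, 10% PLC | 0.10, 0.50 | 0.05, 0.25 | 0.33 × 0.90/0.70 = 42.4% | 0.50 × 0.95/0.90 = 52.8% | 10.3 |

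For scale, the SE of the difference at 175 per arm is sqrt(0.33 × 0.67/175 + 0.25/175) = 5.2 points.

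**3. Adding chart linkage by arm.** With complete charts, the linked stratum returns s and the unlinked stratum 0, so L·s = 33% and 50% is recovered in all three scenarios.

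**4. Incomplete charts, scenario (c).** Assume charts capture 80% of linked SOC men and 95% of linked PLC men.

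- *Chart linkage as a predictor.* SOC: the charted-linked stratum gives 0.40 × 0.66 = 0.264. The other stratum (0.60 of men) has a completers' rate of (0.09 × 0.66)/(0.09 + 0.25) = 0.175, adding 0.105, total 36.9%. PLC: 0.7125 × 0.667 = 0.475, plus 0.2875 × (0.0356 × 0.667)/(0.0356 + 0.1875) = 0.031, total 50.6%. Difference 13.7 points, against 10.3 with baseline data only.
- *Non-attenders without charted linkage counted as failures.* SOC: 0.33 × 0.90 + 0.40 × 0.10 × 0.66 = 32.3%. PLC: 0.50 × 0.95 + 0.7125 × 0.05 × 0.667 = 49.9%. Difference 17.5 points.
- *Chart confirmation demanded of every man, attenders included.* 0.33 × 0.80 = 26.4% vs 0.50 × 0.95 = 47.5%. Difference 21.1 points, inflated towards PLC.

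The first two bracket the true 17.0 in this example, which is a reason to report both. The third shows what a hard chart rule can do when chart completeness differs by arm.

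**5. The other reading of 33% and 50%.** The plan applies these rates to the men left after attrition, so take them instead as completers' rates p. Assume a share f of the missing 20% are unlinked and the rest succeed at p. The rate over all randomized men is then p(1 − 0.2f).

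- f = 50% in both arms: 29.7% vs 45.0%, difference 15.3
- f = 100% in both arms: 26.4% vs 40.0%, difference 13.6
- f = 50% SOC, 100% PLC: 29.7% vs 40.0%, difference 10.3
- f = 100% SOC, 50% PLC: 26.4% vs 45.0%, difference 18.6

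Baseline-only imputation would report 33% vs 50%, difference 17.0, in every case.

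**The case against.** **The text does not say that known failures become successes.** A reader might infer that men charted as unlinked will be imputed as successes. The protocol speaks of imputing missing data and does not say that the composite is imputed as one variable over an observed component. If only VL is imputed and the composite then derived, a man known to be unlinked stays a failure. This objection stands. It does not remove the point: a VL model without linkage still draws linked and unlinked men from the same pool, and Aim 3 is worded in terms of VL success.

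**"We will evaluate the attrition effect by multiple imputation of missing data using baseline characteristics of the individuals" names inputs but excludes none.** That is true, and a separate analysis plan may add more. But the article does state the inputs, and an analysis plan that follows the sentence would leave linkage out.

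**Chart coverage is not certain.** A reader might infer that charts are available for every enrolled man. The lead-in about the exit interview, and the purpose of confirming linkage, leave room for abstraction in attenders only. The consent described under mobile HTS does not mention charts. The wording about enrolled men supports the wider reading but does not settle it.

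**No chart is not proof of no linkage.** Under HIV standard of care, SOC men may seek care wherever they like, while PLC men are accompanied to a clinic. Chart completeness may therefore differ by arm. This stands and shapes the fix.

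**The sizes are driven by assumptions.** Linkage and drop-out rates are assumed, scenario (b) is extreme, scenario (c) departs from the planned 20%, and the shifts run both ways. With equal non-linkage, step 5 gives 2 to 3 points, less than one SE.

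**Conclusion.** The point holds as an improvement to a stated secondary method. The imputation names only baseline inputs although the same article plans to collect a necessary component of the outcome by a route that need not depend on the exit visit. Where drop-out follows linkage and baseline data are weak predictors, the check adds little to the completers' analysis.

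In the illustrations, arm rates are overstated by about 3 points (33.0 against 29.7) to 13 points (62.5 against 50.0). With a true difference of 17.0, baseline-only imputation gives 10.3 to 21.3. On the other reading it reports 17.0 where the value ranges from 10.3 to 18.6. These sizes rest on rates that the documents do not give, and no direction of bias can be claimed.

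Nothing here shows an error in the power calculation or changes the primary test. Aim 3 is touched only if an attrition adjustment is made there, and the protocol does not say that it would be this imputation.

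**What to change.** In Secondary analyses for Aim 2, replace the imputation sentence with wording to this effect:

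- Imputation is done separately by arm, from baseline characteristics (including baseline VL) plus chart-abstracted linkage and retention as predictors. The composite is derived from its imputed or observed components.
- A sensitivity analysis counts non-attenders with no linkage on chart as failures. It is not the main rule, because chart completeness may differ by arm.
- Three- and six-month contact data are not used as common predictors. In the PLC arm, follow-up visits record care documents and medications; in SOC the calls serve only to keep track of the men.

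In Measurement of Aim 2 outcomes, state that chart abstraction includes men who miss the exit visit, where consent allows. If Aim 3 uses attrition-adjusted rates, state that they are these.

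Cost: a few sentences, slightly more analysis work, and dependence on how complete the charts are. On the plain reading of the abstraction plan no new data are needed. If abstraction was meant for attenders only, extending it is extra fieldwork and may need consent.
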